### Secondary outcomes

#### Lymphedema tissue features

These will be determined by means of thermography, a safe, non-invasive imaging method that determines the distribution of body surface temperatures according to physiological and pathological tissue conditions. Inflammation, metabolic subcutaneous tissue changes, and blood supply changes result in temperature gradient changes in the affected area. Thus, different lymphedema stages will be associated to different temperature distribution patterns. A Onepro LT Flir thermographic camera (4800 pixels), with a temperature capture range from – 20 °C to 120 °C will be used to this end. The study participants will be instructed to remain in a standing position, without garments or other trunk and upper limb accessories. Body surface temperatures will be recorded using a thermal camera in the orthostatic position, from the anterior and posterior limb portions, at a 2 m distance. The thermometric images will then be analyzed using the FLIR One***®*** software.

#### Grip strength

This will be evaluated by means of a dynamometer, an instrument widely used to assess handgrip strength. The interviewees will be seated in a chair without armrests with an erect spine, knees flexed at 90°, shoulder positioned in adduction and neutral rotation, elbow flexed at 90°, forearm in half pronation and neutral wrist (or up to 30° extension) [14]. The evaluator supports the weight of the dynamometer and keeps the patient’s arm suspended in the air and the interviewee then performs three bilateral test repetitions. The average of the three measurements will be considered.

#### Health-related QoL

The health-related QoL will be assessed by using two European Organization for Research and Treatment of Cancer (EORTC) questionnaires.

#### Quality of Life Questionnaire Core 30 (EORTC QLQ-C30)

This comprises a specific questionnaire used to assess cancer patients. This instrument comprises 30 questions that derive from functional scales (physical functioning, role functioning, emotional functioning, cognitive functioning, social functioning), symptom/item scales (fatigue, nausea and vomiting, pain, dyspnea, insomnia, appetite loss, constipation, diarrhea, financial difficulties), and global health status/QoL [15].

#### Quality of Life Questionnaire breast cancer-specific (EORTC QLQ-BR 23)

This comprises a specific questionnaire to assess the quality of life of patients presenting breast cancer, consisting of 23 questions divided into functional scales (body image, sexual functional, sexual enjoyment, future perspective) and symptom/item scales (systemic therapy side effects, breast symptoms, arm symptoms, hair loss) [16].

Each scale of both questionnaires scores from 0 to 100. Higher scores in the functional and health-related quality of life (HRQoL) scales indicate a better quality of life, while higher scores in the symptom/item scales translate to a worse quality of life [17]. Both questionnaires have been translated into Portuguese and validated for the Brazilian population [18, 19].

#### Upper limb functionality

Upper limb functionality will be evaluated by the Disabilities of the Arm, Shoulder and Hand Questionnaire (DASH), translated into Portuguese and both validated and adapted for the Brazilian population in 2005 [20]. This questionnaire is widely employed in the evaluation of mild, moderate, and severe shoulder, elbow, and hand disorders. The questionnaire addresses the condition referring to the week before its application and is based on the patient’s ability to perform certain activities, regardless of the used limb. Consisting of 30 questions, the questionnaire evaluates the following domains: physical upper limb function, patient symptomatology, social function, sports practice, music practice, and work activity.

#### Adherence

To assess treatment adherence, participants must fill in a therapeutic diary that will be delivered in the first appointment in which they will be able to notify and grade arm-related symptom intensity through a numerical visual scale (NVS) and write down information they consider relevant concerning the use of compression therapy (such as time of use and adverse events). This resource must be filled out during the 30 days of treatment and given to the therapist during the outpatient consultation.

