### Objectives {7}

The primary aim of this study is to evaluate the effectiveness of a self-adjusting compression garment (ReadyWrap®) in reducing and maintaining upper limb volume in women presenting breast cancer-related lymphedema compared to standard compression therapy. Secondary objectives consist in comparing upper limb volume and tissue changes, muscle strength, functionality, and symptoms, as well as health-related quality of life, while also assessing the incidence of adverse events, treatment adherence, and material and professional costs according to the intervention group.

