#### Group D: Standard compressive mesh intervention

This group will receive the standard upper limb volume maintenance treatment employing a compressive mesh that provides 30 to 40 mmHg of pressure and has an elastic Velcro strap for fixation that will be adapted according to ideal size indications following affected upper limb perimetry measurements. The compressive mesh must be continuously used, removing the mesh only for bathing and night sleeping. After 7 days of adaptation, the research team will contact the patients by phone to monitor possible adverse events and assess the need for face-to-face consultations. Outpatient follow-up and evaluations in face-to-face consultations will take place on the 1st and 30th day after adaptation.

Participants in each intervention group will be followed and reassessed 6 and 12 months after study enrollment to verify long-term outcome measures. At the end of this period, the standard compressive mesh will be adapted and provided free of charge according to the applied institutional routine.

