### Strategies to improve adherence to interventions {11c}

With the aim of improving treatment adherence, the volunteers will receive a therapeutic diary for use in the first 30 days, in which they must notify exercise performance, garment use, and any arm symptoms during treatment daily. In addition, a face-to-face consultation for the phase 1 groups (A and B) and a teleconsultation for the phase 2 groups (C and D) will be performed within 7 days of study inclusion.

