#### Adverse events

Adverse events will be verified during the first and second treatment phase through therapeutic diary reports and notes regarding the occurrence and intensity of the following symptoms: contact dermatitis, skin infection, uncompensated arterial hypertension, and upper limb volume worsening by 10% of the initial volume, among other unforeseen effects. In addition, all participants will also be provided with a telephone contact that will serve as a communication channel between participants and therapists for reporting adverse events, unpleasant symptoms, and/or questions about the lymphedema treatment, as well as any guidance, when relevant.

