## Data collection and management

### Plans for assessment and collection of outcomes {18a}

The data collection will take place through interviews, physical examinations, and medical record analyses. All data will be collected by experienced physiotherapists. The interviews will consist of semi-structured questionnaires produced by the researchers, in addition to questionnaires validated for the Brazilian population. Regarding the physical examination, the volume of the upper limb with lymphedema will be evaluated using perimetry, tissue characteristics using thermography, and muscle strength will be evaluated using dynamometry. These assessment resources will be used for all participants included in the study and performed before and after the initial 30 days of treatment and during follow-up (6 and 12 months). Data regarding oncological treatment and lymphedema treatment history will be obtained from physical and electronic medical records.

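### After the 30-day diary ends, no systematic adverse-event collection is stated, although follow-up runs to 12 months and adverse-event incidence by group is a secondary objective

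*Protocol article*

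**What the plan says.** - **Objective.** Objectives {7} lists among the secondary aims "assessing the incidence of adverse events, treatment adherence, and material and professional costs according to the intervention group". It gives no time window.
- **Instrument.** The Adverse events section states: "Adverse events will be verified during the first and second treatment phase through therapeutic diary reports and notes". Adverse event reporting and harms {22} repeats this.
- **Duration of the instrument.** Strategies to improve adherence {11c} says that "the volunteers will receive a therapeutic diary for use in the first 30 days". The Adherence section agrees: "This resource must be filled out during the 30 days of treatment and given to the therapist during the outpatient consultation".
- **Second channel.** The Adverse events section adds that "all participants will also be provided with a telephone contact that will serve as a communication channel between participants and therapists for reporting adverse events". No end date is given, and the participant has to make the call.
- **Follow-up.** The last paragraph under Group D reads: "Participants in each intervention group will be followed and reassessed 6 and 12 months after study enrollment to verify long-term outcome measures". Plans for assessment and collection of outcomes {18a} has perimetry, thermography and dynamometry "performed before and after the initial 30 days of treatment and during follow-up (6 and 12 months". It also provides for interviews, questionnaires and medical records, and does not mention adverse events.
- **Abstract.** The Methods paragraph names adverse effects among the things assessed, next to limb inspection and palpation. It gives no instrument or visit for them.

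**The concern.** Incidence is a count over an interval, so it needs an instrument that covers the interval. Here the named instrument stops at day 30 and the study continues for eleven more months. A skin infection or dermatitis that starts and resolves between the 30-day and 6-month visits, or between the 6- and 12-month visits, enters the data only if the woman telephones or if someone asks about it. The article describes no one asking.

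The comparison between groups is also at stake. Participants and physiotherapists know the allocation (Concealment mechanism {16b}, Who will be blinded {17a}). Where reporting is voluntary, women with a new device and women with the familiar standard may telephone at different rates. The article gives no information on whether they would, or in which direction. No data monitoring committee (section {21a}) and no audit (section {23}) is planned, so no other stated safeguard closes the gap.

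**Working it through.** The plan gives no figure of its own to reproduce here. The check has three parts.

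**1. Time covered by the diary**

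Inputs: diary length 30 days (sections {11c} and Adherence); follow-up 12 months (last paragraph under Group D, and section {18a}).

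- Share of follow-up without a diary = (follow-up days − 30) / follow-up days.
- With 365 days: (365 − 30)/365 = 335/365 = 91.8%.
- With 360 days: 330/360 = 91.7%. In months: 11/12 = 91.7%.

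So about 92% of calendar follow-up has no diary.

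**2. What that share does and does not say about events**

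Let f be the fraction of a woman's events that fall after day 30, and r the fraction of those that reach the trial by telephone or otherwise. The share missed is f × (1 − r). The article gives neither f nor r. Each can lie anywhere from 0 to 1, so the share missed can too, and no undercount can be computed. For the group comparison, the observed ratio of late events (experimental to standard) equals the true ratio multiplied by r(experimental)/r(standard). If reporting is equal, the ratio is preserved but absolute incidence is too low whenever r is below 1. If reporting differs, the ratio is distorted by that factor.

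**3. Which events and which groups are affected**

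By event:

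- *"upper limb volume worsening by 10% of the initial volume"*: can be derived from perimetry at 6 and 12 months. Not lost at those visits.
- *Skin infection, contact dermatitis, uncompensated hypertension, unforeseen effects*: no instrument stated after day 30 other than the telephone line.

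By phase:

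- *Phase 1 (groups A and B, 72 of the planned 144 women).* Both interventions last 30 days, so the diary covers all of the described treatment. Only late events are affected.
- *Phase 2 (groups C and D, the other 72).* No duration is stated. Group C is described as similar to group A, whose treatment lasts 30 days. Yet section {18a} calls the first 30 days the initial part of treatment, and the last paragraph under Group D has the standard mesh supplied only once the 12-month follow-up is over. The second pair of statements suggests wear beyond day 30. If so, the undertaking to verify events during the second treatment phase cannot be met by a diary that ends at day 30.

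The article does describe active enquiry in one place: in phase 2 the team telephones after 7 days to look for possible adverse events. That falls inside the diary window, and no equivalent is described later.

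**The case against.** The strongest reply is that the article does not confine adverse-event assessment to the diary. The Abstract lists adverse effects among the assessments and includes inspection and palpation. Section {18a} provides for semi-structured interviews, whose content is not shown, and for medical records. Section {21a} has the physiotherapists act on effects that participants report, with no 30-day limit. A journal article condenses the full protocol, and a visit-level form may well exist there. Phase 1 is covered throughout treatment, continued wear in phase 2 is inferred, and nothing says that incidence will be presented as a 12-month figure; section {21b} plans a 30-day analysis. With 115 women included by May 2023, a change also comes late for many.

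Much of this stands, and it limits the point:

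- A reader might infer that adverse events are undercounted for 92% of follow-up, or that about 11 of every 12 events are lost. The documents support neither. The first turns a share of time into a bias. The second needs a constant event rate over 12 months, which nothing in the article supports and which fits poorly where treatment ends at day 30.
- A reader might also infer that nothing is collected after day 30. That is wrong: volume is measured, the telephone line stays open, and signs present on the day of a visit could be seen.

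What does not stand is that these items amount to collection of incidence. Inspection at month 6 or 12 does not show an event that has resolved. Section {18a} limits the record review to oncological treatment and lymphedema treatment history. Section {21a} acts on what participants volunteer. Nor is this mere silence from condensing: the article names the instrument, gives its end date, and lists the examinations made at the later visits.

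**Conclusion.** The point holds in a limited form. The adverse-event window is not defined and does not match the 12-month follow-up. After day 30, three of the four named events, and any unforeseen ones, have no stated systematic collection. About 92% of follow-up time (335/365 days) has no diary; how many events that costs, and whether it favours either group, cannot be determined from the article.

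The weight falls mainly on phase 2. It rests on reading section {18a} and the last paragraph under Group D as meaning that allocated compression continues past day 30. If phase 2 treatment in fact ended at day 30, the gap would concern late events only, as in phase 1. The conclusion also assumes that the full protocol, which is not shown, contains no adverse-event form for the later visits. If it does, describing it would settle the matter.

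**What to change.** 1. In the Adverse events section and in section {22}, add one short checklist at the existing 30-day, 6-month and 12-month visits in all four groups: the named events plus other, each with an onset date, covering the time since the last visit. Check answers against the medical record, and widen the record review in section {18a} to allow this.
2. State the adverse-event window for each phase. Reconcile the group C description, the last paragraph under Group D and section {18a}, so that it is clear how long allocated compression lasts in phase 2.
3. Report incidence by group separately for days 1–30 and for day 31 to month 12, with the number of women asked at each visit as the denominator. The first window has diary plus checklist and the second only the checklist, so rates in the two windows should not be read as equally well ascertained.
4. For women already past these visits, limit any claim about solicited incidence to days 1–30.

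The cost is one short form at visits that already take place, and a small amendment. The downside is that recall over about six months is less precise than a daily diary; the record check offsets this for events that were treated.

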#### Adverse events

Adverse events will be verified during the first and second treatment phase through therapeutic diary reports and notes regarding the occurrence and intensity of the following symptoms: contact dermatitis, skin infection, uncompensated arterial hypertension, and upper limb volume worsening by 10% of the initial volume, among other unforeseen effects. In addition, all participants will also be provided with a telephone contact that will serve as a communication channel between participants and therapists for reporting adverse events, unpleasant symptoms, and/or questions about the lymphedema treatment, as well as any guidance, when relevant.

#### Treatment costs

The following will be considered in the cost analysis: treatment time, number of sessions, material expenses per patient in each treatment phase, transportation expenses to the hospital from home, and food expenses in the hospital. The patient’s expenses will all be considered, including companion expenses, if any.

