#### Group B: Standard compressive bandaging intervention

This group of participants will receive the standard compressive bandaging treatment for upper limb volume reduction. The compressive bandaging consists of adapting low-elastic bandages placed in layers (multilayer) throughout the affected limb. The upper limb will first be cleaned and hydrated and a tubular mesh will then be worn for protection and for minimizing the risk of allergic reactions. The foams will then be adapted to give the limb a cone shape and soften bone points, contributing to regular pressure distribution. Finally, the bandages will be adapted from the distal to the proximal part. The compressive bandaging will be used continuously for 30 days, changed twice a week in face-to-face consultations. The evaluations will take place on the 1st, 7th, and 30th day after adaptation.

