### Provisions for post-trial care {30}

If an increase of over 10% of the initial volume of the upper limb presenting lymphedema is observed during the 30-day reassessment after participant inclusion, compromising patient functionality and/or quality of life, the participant will be directed to the standard treatment offered by the institution’s physiotherapy service. At the end of the study, regardless of the allocation group and results, participants will be directed to lymphedema treatment according to the institutional routine.

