### Composition of the data monitoring committee, its role and reporting structure {21a}

A data monitoring committee was not formed for this study. This decision was made based on the absence of serious adverse effects by the applied treatments, both in the experimental treatment and the control, which is the institution’s standard. In any case, control and notifications by the research physiotherapists involved in the study of possible adverse effects and undesirable symptoms reported by the volunteers will be performed. If unwanted effects resulting from the treatment are observed, the participant will withdraw from the study and the institutional routine will be conducted, depending on the situation, and all necessary medical support will be provided.

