## Discussion

This study will evaluate the effectiveness of the self-adjusting garment (ReadyWrap®) in the treatment of lymphedema secondary to breast cancer in Brazilian women compared to the gold standard treatment for volume reduction (phase 1) and maintenance (phase 2) comprising a compressive bandaging and a compressive mesh, respectively. Outcome results will provide data based on both quantitative responses and self-reported participant outcomes. The study will also assess the cost-effectiveness of the ReadyWrap® treatment versus standard care. Finally, after the data analysis, we expect to propose another compression modality for the treatment of this extremely complex and impactful condition.

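### The listed cost items include no hospital-side item for adverse-event care or for treatment after suspension, and withdrawal can end cost capture, so the cost comparison by arm can be biased

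*Protocol article*

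**What the plan says.** Under Treatment costs, the protocol article names the items to be analysed: "treatment time, number of sessions, material expenses per patient in each treatment phase, transportation expenses to the hospital from home", and food at the hospital. It then adds: "The patient’s expenses will all be considered, including companion expenses, if any". No time horizon is given.

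Objectives {7} makes this a secondary aim, comparing "treatment adherence, and material and professional costs according to the intervention group". The Abstract and the Discussion go further: "The study will also assess the cost-effectiveness of the ReadyWrap® treatment versus standard care".

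Other sections foresee care beyond the planned course:

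- Criteria for discontinuing {11b} and Adverse event reporting {22} provide for early suspension, for example for allergic reaction, poor adaptation, increased limb volume or infection.
- Provisions for post-trial care {30}: after a volume increase of over 10% at the 30-day reassessment that compromises functionality or quality of life, "the participant will be directed to the standard treatment offered by the" institution's physiotherapy service.
- Section {21a}, on the data monitoring committee: if unwanted effects of treatment are seen, "the participant will withdraw from the study and the institutional routine will be conducted, depending on the situation, and all necessary medical support" is to be given.

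Section {20c} states that outcomes are assessed by intention to treat.

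**The concern.** A cost comparison between two devices should carry the cost of failure and harm as well as the cost of delivery. Here the list names delivery items, while the protocol itself expects some women to be suspended, redirected or treated for adverse effects. At a public hospital, much of the cost of that care (sessions, bandages, staff time, medical care) falls on the provider. The sentence on patient expenses does not reach it.

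The withdrawal statement in {21a} adds to the problem. The women whose care becomes more expensive are the ones who may leave the data. If that happens more often in one arm, the difference in mean cost is distorted.

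The matter is not peripheral to the trial's message. The Background presents fewer individual consultations, with control of the lymphedema maintained, as an economic advantage of self-adjusting garments. In phase 1 the institutional standard is bandaging, "changed twice a week in face-to-face consultations". Treatment after a suspended ReadyWrap course could therefore consist of the very visits that the garment is credited with avoiding.

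**Working it through.** The article states no cost figure, so there is none to reproduce. The check is a comparison of sections, followed by an illustration in session counts.

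**1. Listed items against foreseen care**

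| Care foreseen | Where | Item under Treatment costs |
|---|---|---|
| Planned course: sessions, material, time | Phase 1 and 2 descriptions | Named |
| Travel, food, companion | – | Named, as patient expenses |
| Institutional treatment after suspension or redirection, hospital side | {11b}, {30}, {21a} | Not named; general wording on sessions and material might be read to include it |
| Medical care of adverse events, hospital side | {21a}, {22} | Not named |
| Any of these after withdrawal from the study | {21a} | Not addressed; {20c} says intention to treat |

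**2. Scheduled phase 1 sessions**

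- ReadyWrap: face-to-face evaluations on days 1, 7 and 30, so 3.
- Bandage: two changes a week for 30 days, 2 × 30/7 = 8.57, taking evaluations to coincide with changes.
- Scheduled saving: 8.57 − 3 = 5.57 sessions.

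**3. Illustration**

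Assumptions, none of them from the article:

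- fA (ReadyWrap) and fB (bandage) are the proportions suspended.
- A suspended ReadyWrap woman has had 2 sessions, and a suspended bandage woman half of hers (4.29).
- Each then has one 30-day bandaging course of 8.57 sessions, and none of it is counted.

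Formulas:

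- Counted mean, ReadyWrap: 3(1 − fA) + 2fA = 3 − fA
- Counted mean, bandage: 8.57(1 − fB) + 4.29fB = 8.57 − 4.29fB
- Full mean: counted mean + 8.57f in each arm
- Omitted from the difference: 8.57 × (fA − fB)

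| fA, fB | Counted saving | Full saving | Omitted | Counted / full |
|---|---|---|---|---|
| 5%, 5% | 5.41 | 5.41 | 0 | 1.00 |
| 10%, 0% | 5.67 | 4.81 | 0.86 | 1.18 |
| 20%, 5% | 5.56 | 4.27 | 1.29 | 1.30 |
| 30%, 10% | 5.44 | 3.73 | 1.71 | 1.46 |

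With equal rates the difference is unaffected, although both arm totals are too low.

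**4. Early stopping separated from omitted treatment**

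Truncation alone changes the scheduled saving by 4.29 lost bandage sessions per suspension against 1 lost ReadyWrap session, that is, by fA − 4.29fB:

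- 10% against 0%: +0.10
- 20% against 5%: 0.20 − 0.21 = −0.01
- 30% against 10%: 0.30 − 0.43 = −0.13

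So truncation moves the saving little, and in the last two cases it slightly lowers the saving credited to ReadyWrap. Nearly all of the error in the table comes from the assumed full bandaging course.

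**5. Could the saving reverse?**

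With no bandage suspensions, the full means are equal when 3 − f + 8.57f = 8.57, so f = 5.57/7.57 = 74% suspended on ReadyWrap. The sample size section adds 20% for losses and interruptions together.

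**6. Phase 2**

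Both arms have face-to-face visits on days 1 and 30 and a day-7 telephone call. There is no scheduled session saving to overstate. What can still be missed is adverse-event care and treatment after suspension.

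**The case against.** The strongest reply is that the text is not as narrow as it may look. A reader might infer that only delivery of the allocated treatment is costed. The article does not say so: sessions and material are listed per patient, without restriction to the allocated device, and a bandaging session after suspension could be counted as a session. Patient travel, food and companion costs of such visits fall under the general sentence on patient expenses. Intention to treat is planned, each group is followed to 6 and 12 months, and lymphedema treatment history is already taken from medical records ({18a}).

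A reader might also infer that a device stopped early is scored as cheaper and that the comparison therefore favours the device that fails more. The documents do not support this as a general statement. The garment is sized and supplied at the start, so stopping it probably recovers little material cost, and step 4 shows that truncation alone can work against ReadyWrap. Redirection under {30} happens at the 30-day reassessment, when the course is complete, so it is not early stopping. Nor does any section say that every suspended woman has a full bandaging course; {21a} leaves it to the situation.

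Finally, a journal article may leave costing detail to a fuller document, and a missing horizon alone would be no finding.

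These points remove any claim about direction and most of the claim about size. Two things stand. The article does fix a list of items, and that list has nothing for hospital-side adverse-event care and nothing explicit for treatment after suspension. And {21a} takes affected women out of the study without saying how that fits with {20c}.

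**Conclusion.** The point holds in a limited form. Followed as written, the cost analysis can miss hospital costs of adverse events and of treatment after suspension or redirection, and {21a} can end capture for the women concerned. The comparison by arm can then be biased when suspension or adverse-event rates differ, which matters more once it is presented as cost-effectiveness.

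Neither direction nor size can be established, because the article gives no suspension rates, adverse-event rates or unit costs. The phase 1 figures of 0.9 to 1.7 omitted sessions per randomised woman rest on assumed rates and on an assumed full bandaging course for every suspended woman. Even then the session saving shrinks to between 3.7 and 4.8 and does not reverse. This concerns a secondary outcome; the primary volume outcome and the sample size are untouched.

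**What to change.** Under Treatment costs, state that costs are counted per randomised woman, by allocated arm, over stated horizons of 30 days and 12 months, whether or not treatment was stopped. Add three items:

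- hospital sessions and material used after suspension or redirection;
- unscheduled consultations;
- care of adverse events.

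Take them from the medical records already used under {18a}. Reconcile {21a} with {20c}, so that stopping treatment does not stop collection of cost data unless the woman withdraws consent. This concerns data collection only, not which treatment she receives.

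The change needs some wording and a little more extraction at a single site, with no new visits or participants. The downside is that extra work and possibly less favourable cost figures.
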